### Assessments and procedures

There are three trial assessments (see Fig. 1 for the flowchart): a baseline assessment after randomization and before the start of the intervention, a second assessment 14 weeks after baseline, and a follow-up assessment 24 weeks after baseline. The baseline and second assessments consist of web-based questionnaires, which are completed at home, and several measurements in the hospital (e.g. MRI, magnetoencephalography, neurocognitive testing and neurological examination). The questionnaires and measurements are explained in further detail at the endpoints section. The follow-up assessment only consists of web-based questionnaires.

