(5) No oncological treatment for at least two months prior to inclusion	(5) Pregnancy or given birth in the past three months
(6) No signs of radiological or clinical tumour progression at the time of inclusion	(6) Pharmacological treatment for fatigue, started in the past three months
(7) Able to speak, read and write Dutch	(7) Karnofsky Performance Status score <70 [39]
(8) Access and ability to use the internet	(8) Corticosteroid use
(9) Written informed consent	

Abbreviations: *CIS* Checklist Individual Strength, *BDI-PC* Beck Depression Inventory – Primary Care

After signing for informed consent and completing the screening procedure, the patient will be randomized to the BCBT intervention or to the WLC group with the use of the web-based computer program, Castor EDC [41]. This program automatically randomizes the patient to one of the two conditions. To keep the number of patients randomized to the two arms balanced throughout the trial, the program uses block randomization with a block size of two and four in random order. A block of two consists of one randomization to the BCGT group and one randomization to the WLC group in random order. A block of four consists of two BCGT randomisations and two WLC group randomisations in random order [42]. After the screening process, the patient is informed on the outcome of the randomization.

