### Statistical analysis

The final analysis is conducted on an intention-to-treat basis. Efficacy of the intervention will be concluded based on the posterior probability as outlined in the previous paragraph. Cohen’s *d* will be calculated as an effect size for CIS-fatigue scores where multiple imputation will be used to deal with missing second measurements. Sensitivity analyses will be performed to assess the robustness of the standardized effect size under different imputation strategies.

In addition, analysis of covariance (ANCOVA) will be performed for the secondary outcomes of the second assessment, with the baseline score on the dependent measure as covariate and group allocation as the fixed factor. A *p*-level of 0.05 will be used. Longer-term follow-up effects will also be tested using ANCOVA, with the baseline score on the dependent measure as covariate. Different tumour types will be added to the model as covariates. Cohen’s *d* will be calculated as effect sizes for the secondary outcomes.

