Potential limitations of the current study design are the inability to blind participants and researchers for the given intervention and the lack of a true placebo condition in the WLC group. These are issues that in general arise in all psychotherapy trials [66]. In this study, patients randomized to the WLC group can be treated for fatigue after the follow-up measurements. It has been hypothesized that a WLC could both result in a placebo and a nocebo response. Provided reasons include that a WLC with future treatment could provide patients with hope for future symptom reduction thus inducing a placebo response, but also that a WLC might result in a nocebo response because the patient has already expressed interest in the therapy and therefore is less motivated to change their behaviour awaiting the promised treatment [66–68]. However, not including a waiting list condition in research in this population is questionable, since patients suffer from severe fatigue with currently no other effective treatment available. Considering this, a WLC seems to be appropriate for this group of vulnerable patients.

The *GRIP on fatigue* trial will provide information on the efficacy of BCBT compared to a WLC in reducing severe fatigue in patients with diffuse glioma. Secondary outcome measures will include different questionnaires concerning HRQOL, subjective cognitive impairments and symptoms such as depression and anxiety. We additionally aim to investigate exploratory measurements that may relate to treatment response and ultimately predict treatment outcome. If proven effective, we aim to offer the intervention as part of usual care for this group of patients.

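### Baseline questionnaires come after randomisation, and probably after patients know their arm, yet serve as ANCOVA covariates for the secondary and follow-up outcomes

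*Protocol article*

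**What the plan says.** Order of steps. Recruitment, screening and randomization: "After signing for informed consent and completing the screening procedure, the patient will be randomized to the BCBT intervention or to the WLC group". The same section ends: "After the screening process, the patient is informed on the outcome of the randomization". Assessments and procedures then defines the first trial assessment as "a baseline assessment after randomization and before the start of the intervention". The article does not say that disclosure waits until baseline is finished.

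Mode and blinding. On how baseline is collected: "The baseline and second assessments consist of web-based questionnaires, which are completed at home", with further measurements in the hospital. The Discussion lists as a limitation "the inability to blind participants and researchers for the given intervention", and mentions the hypothesis that a waiting list may provoke a placebo or a nocebo response.

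Use of baseline. Statistical analysis specifies ANCOVA for the secondary outcomes at the second assessment, "with the baseline score on the dependent measure as covariate and group allocation as the fixed factor". For the threshold it says "level of 0.05 will be used" (a p-level). It adds: "Longer-term follow-up effects will also be tested using ANCOVA, with the baseline score on the dependent measure as covariate".

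Primary decision. Termination for efficacy or futility bases efficacy on the posterior probability that mean CIS-fatigue is lower under BCBT. No baseline term is stated there.

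**The concern.** ANCOVA in a randomised trial estimates the treatment effect without bias because a covariate measured before allocation cannot depend on the arm. A covariate measured after allocation is known loses that guarantee. Depression, anxiety, sleep quality and HRQOL are all self-reported, and a patient's answers may move on learning of a place on the waiting list or in therapy. The model treats any such movement as a pre-existing difference between the arms and adjusts for it, so part of the reaction to allocation enters the estimated effect with its sign reversed.

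At stake are the secondary conclusions at 14 weeks and the follow-up conclusions at 24 weeks. The damage cannot be undone in the analysis, because for most secondary outcomes the article describes no measurement from before randomisation. CIS-fatigue is an exception, since the CIS is completed at screening.

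**Working it through.** **The plan's own figures.** No stated figure depends on when baseline is taken. The sample-size inputs reproduce: 40 / (1 − 0.20) = 50 per arm, or 100 in total. A fixed design at d = 0.7 (two-sided 5%, 80% power) needs 34 evaluable per arm by the noncentral t, and 34 / 0.80 = 42.5, which rounds up to the stated 43.

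**Inputs for this point**
- 40 evaluable patients per arm: Sample size calculation and Bayesian design.
- Nominal p-level 0.05, taken as two-sided: Statistical analysis.
- rho, the correlation of baseline with outcome: not in the article; assumed 0.3, 0.5, 0.7.
- s, the between-arm shift in reported baseline caused by knowing the arm, in SD: not in the article; assumed 0.2 and 0.3.

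**Formula.** With baseline X, outcome Y and within-arm slope b, the adjusted difference is

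D = (Ȳ_BCBT − Ȳ_WLC) − b × (X̄_BCBT − X̄_WLC).

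With equal SDs at both times, b ≈ rho. If allocation moves X by s between the arms and leaves Y unchanged, D is off by rho × s in absolute size.

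**Bias and error rate.** Simulated with no true treatment effect, 40 per arm, 4,000 runs per cell:

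| rho | s | Bias = rho × s (SD) | Actual error of the nominal 5% test |
|---|---|---|---|
| 0.3 | 0.2 | 0.06 | 5.3% |
| 0.5 | 0.2 | 0.10 | 7.8% |
| 0.7 | 0.2 | 0.14 | 13.5% |
| 0.3 | 0.3 | 0.09 | 7.3% |
| 0.5 | 0.3 | 0.15 | 12.1% |
| 0.7 | 0.3 | 0.21 | 24.8% |

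With s = 0 the simulated error is 4.9–5.4%, which is nominal.

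**Check by hand.** The standard error of D is about √[(1 − rho²) × 2/40].
- rho = 0.5, s = 0.2: √(0.75 × 0.05) = 0.194; 0.10 / 0.194 = 0.52; P(Z > 1.44) + P(Z < −2.48) ≈ 0.081. The simulation gave 7.8%.
- rho = 0.3, s = 0.2: √(0.91 × 0.05) = 0.213; 0.06 / 0.213 = 0.28; P(Z > 1.68) + P(Z < −2.24) ≈ 0.059. The simulated 5.3% has a Monte Carlo standard error of √(0.053 × 0.947 / 4000) ≈ 0.35 percentage points, so the true value in this cell is probably nearer 6%.

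**Direction.** Take CIS-fatigue, where lower is better. Disappointment on the waiting list raises X̄_WLC and hope in the BCBT arm lowers X̄_BCBT. Either makes X̄_BCBT − X̄_WLC negative, so −b × (X̄_BCBT − X̄_WLC) is positive and D moves against BCBT. The opposite shift moves D in favour of BCBT. The same holds, with signs reversed throughout, for scales on which higher is better.

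**Reach.** ANCOVA is specified for the secondary outcomes at 14 weeks and for longer-term effects. The primary rule compares 14-week means, so s does not enter it.

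**The case against.** Several points on the other side are sound.

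- **The primary result.** A reader might infer that the planned effect of 0.7 is distorted, or that the sequential one-sided error of the efficacy decision is inflated. The article does not support this, because the stated rule has no baseline term. Baseline could reach the primary effect size only through the multiple imputation used for Cohen's d, and the article does not say whether it is in the imputation model.
- **False claims of benefit.** A reader might assume that the bias flatters BCBT. The most obvious reactions to allocation, if they affect baseline alone, work against BCBT. The error rates above are two-sided and should not be read as rates of false efficacy.
- **Disclosure before baseline is inferred.** No single sentence says it, and the flowchart is not available here. Baseline after randomisation is explicit, however, and nothing indicates that the allocation is held back.
- **The shift is assumed.** The Discussion reports the placebo and nocebo idea as a hypothesis about waiting for treatment. It is not evidence that baseline answers change at once. This limits the claim to a risk of unknown size and leaves the design exposure in place.
- **The 14-week clock starting at baseline.** This applies to both arms alike, and the article gives no figures from which harm could be shown, so it adds nothing to the point.

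**Conclusion.** The point holds, limited to the secondary ANCOVAs at 14 weeks and the longer-term ANCOVAs. The order of steps is a stated design choice and cannot be put down to the article being condensed. It exposes self-reported covariates to the allocation they are meant to be independent of.

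Under the assumed ranges the bias is 0.06–0.21 SD, and a nominal 5% test has an actual error of about 5–25%. These figures rest on the assumed s and rho, on 40 evaluable patients per arm, on the outcome not shifting with the baseline, and on patients knowing their arm when they answer. The direction of the bias cannot be predicted.

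This is a should-fix. It would rank higher if the primary efficacy rule used baseline, but as written it does not.

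**What to change.** 1. Have at least the web-based baseline questionnaires completed and locked before the patient is randomised in Castor. Alternatively, withhold the allocation from the patient until baseline is complete, which would also cover the hospital measurements. The cost is a protocol amendment and a short delay in randomisation or disclosure. Sample size, alpha and power do not change, and the questionnaires are already done online at home.
2. For any follow-up ANCOVA of CIS-fatigue, use the pre-randomisation screening score as the covariate for every patient. Using it only for those already enrolled would put two covariate definitions in one model. The screening score is confined to 35–56 by the entry criterion, so it may gain little precision. It does nothing for the other secondary outcomes.
3. Because some patients entered under the present order (twelve at submission of the article), report the secondary ANCOVAs with a sensitivity analysis without baseline adjustment. Its cost is precision: the variance is larger by about 1/(1 − rho²), that is 1/0.91 = 1.10, 1/0.75 = 1.33 and 1/0.51 = 1.96 at rho of 0.3, 0.5 and 0.7.
4. State whether the post-randomisation baseline enters the multiple imputation for the primary Cohen's d.

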**Fig. 1 Fig1:**
[figure not shown]
Flowchart of the trial

All patients will be treated in concordance with national and regional glioma clinical practice guidelines of the National Dutch Working Group on Neuro-Oncology [1]. Patients are asked not to follow any other interventions or use pharmaceuticals aimed at treating fatigue during trial participation. Patients assigned to the WLC group are on a waiting list and will have the opportunity to do the BCBT program after the follow-up period (see Fig. 1). Patients can withdraw from the study at any time for any reason. The researcher can withdraw patients from the study in case of tumour progression or incorrect enrolment. Patients that drop out or are withdrawn are asked to still conduct the second and follow-up assessments.

### Intervention: GRIP on fatigue

*GRIP on fatigue* is a multimodal Dutch intervention with therapist sessions and online modules with therapist feedback. BCBT for CRF in patients with a brain tumour is directed at the beliefs and behaviour of the patient that contribute to the persistence of fatigue.

The intervention lasts 12 weeks. There are five patient–therapist sessions, of which those at the start and finish of the intervention are face to face. The other sessions can be either face-to-face or via secure video consultation, depending on the patients’ preferences. This is combined with five to eight web-based therapy modules delivered via the web portal Minddistrict (www.minddistrict.nl, CE marking 2017/590-01) hosted by Intermax (SO27001 and NEN-7510 certified). The patient is supported by messaging and feedback from the therapist within the online portal. This portal is available via a web browser on the computer or via an application for tablet and mobile phone.

The information and assignments are based on several evidence-based CBT interventions in different populations targeting fatigue by our research group [27, 43, 44]. These interventions have been adapted by experts on brain tumours and CRF to target patients with a brain tumour. The intervention is based on the assumption that having a brain tumour and/or the operation and treatment may initially trigger fatigue, but that other factors such as sleep disturbance, anxiety, physical inactivity, and dysfunctional thoughts about fatigue are responsible for the persistence of fatigue [13, 23, 43]. The module on fear of recurrence is based on the Conquer Fear program, which has shown to be effective in reducing fear of recurrence in comparison to relaxation training [45]. It is expected that patients spend approximately one hour per day on completing the online intervention.

As there are many individual differences in fatigue maintaining cognitive-behavioural factors, patients who are treated with BCBT undergo assessments to determine the relevant fatigue-maintaining factors and select the right treatment modules addressing these factors. Those instruments form an integral part of the intervention and include a set of questionnaires, actigraphy for fourteen consecutive days and simultaneously keeping a sleep–wake diary on seven consecutive days before the intervention starts. With actigraphy, two different activity patterns will be distinguished: relatively active or low active. The instruments are used for tailoring the treatment, for example the module *Activity regulation* will be personalized with regards to the activity pattern of the patient. Table 2 gives an overview of all modules of the intervention and their content. Some of the modules are optional and only indicated with specific scores on the relevant questionnaires.

**Table 2 Tab2:** Content of the online modules and assessments

Online modules	Assessments
*1. Introduction and goals* The patient formulates positive and tangible goals, which consist of activities they want to do when no longer severely fatigued.	
*2. Sleep and rest* The patient makes a sleep schedule and keeps an online diary with sleep and wake times. A regular sleep–wake cycle and sleep hygiene are discussed. Instructions are given on how to improve these.	- Sickness Impact Profile (subscale sleep and rest) [46] - Registration of bedtime, wake-up time and sleep during the day for seven consecutive days
3. *Fatigue-related cognitions* Loss of control over fatigue symptoms and thoughts, fatigue catastrophizing and dysfunctional thoughts are assessed. The patient does exercises to address and change their dysfunctional thoughts and keeps an online diary about these thoughts. Patients learn to focus less on fatigue.	- Fatigue Catastrophizing Scale [47] - Illness Management Questionnaire factor III [48] - Self Efficacy Scale Fatigue [49]
*4. Activity regulation* The patient with a ‘relatively active’ activity pattern learns to distribute activities more evenly. Then both ‘relatively active’ and ‘low active’ patients systematically increase their physical activity with a graded activity program with walking or cycling. They track their daily progress in an online diary. They learn how to solve problems with activity regulation. The module aims to change activity-impeding beliefs and increase the physical activity level of patients.	- With actigraphy (actometer around the ankle for 14 consecutive days) the level of activity is objectified [50]. The activity pattern will be rated as ‘Low active’ or ‘Relatively active’.
*Submodule 4A: Regulation of social activities (optional)* The relationship between cancer, fatigue and a reduction of social activities as well as cognitions about social activities are assessed. The patient increases his/her social activity level.	- Sickness Impact Profile (*indication for this optional submodule: score subscale social activities ≥ 100*) [46]
*Submodule 4B: Regulation of mental activities (optional)* The patient learns about cognitive deficits and how to deal with them. The patient increases their mental activity level.	- Checklist Individual Strength *(indication for this optional submodule: score subscale concentration ≥ 18)* [36]
*Submodule 4C: Going back to work (optional)* The patient makes a plan to return to work or increase working hours.	*(indication for this optional submodule: if the patient has set a goal to return to work or increase working hours)*
*5. Fear of disease progression (optional)* Thoughts and situations that trigger fear regarding the future or tumour growth are assessed. The patient learns to be more accepting towards anxious feelings and to handle these feelings with exercises based on detached mindfulness, meta-cognitive therapy and exposure.	- Fear of Progression Questionnaire *(indication for the module: score ≥ 34)* [51] - Beck Anxiety Inventory *(indication for the module: score ≥ 36*) [52]
*6. Social support (optional)* Reactions of the partner and significant others to fatigue are assessed. Perceived discrepancy between actual and desired social support, experiences with negative social interactions and unrealistic expectations of others are assessed. The goal of this module is to support emotional independence of others and to become more assertive, as far as fatigue is concerned.	- Social Support List, subscale discrepancy *(indication for the module: score ≥ 50*) and subscale negative interactions (*indication for the module: score ≥ 14*) [53]
*7. Living with a brain tumour (optional)* This module focuses on uncertainty about the future and how one can deal with the fact that one has an incurable disease. Several elements from meaning-centred psychotherapy, well-being therapy and writing therapy are used to help the patients to deal with the disease trajectory.	- Illness Cognition Questionnaire, subscale acceptance (*indication for the module: score* ≤ 12) and subscale helplessness (*indication for the module: score ≥ 14*) [54] - Impact Event Scale, subscale avoidance (*indication for the module: score ≥ 10*) and subscale intrusion (*indication for the module: score ≥ 10*) [55]
*8. Realizing goals* The patient looks back at the goals set in the first module and makes a plan to realize these goals. The intervention is evaluated.	

The intervention will be provided by two to four trained and experienced cognitive-behavioural therapists, working at the Expert Center for Chronic Fatigue of the Amsterdam UMC, a tertiary treatment centre for fatigue. Every patient is assigned to one therapist, based on the availability of the therapist. The therapists are trained in delivering interventions on fatigue and this intervention specifically. They will be supervised every two weeks by a therapist with experience in BCBT in patients with a brain tumour.

### Primary and secondary endpoints

The primary outcome measure is the CIS-fatigue score at the second assessment, 14 weeks after baseline. The eight CIS-fatigue items are rated on a seven-point Likert scale with a total score ranging from 8 to 56. A score ≥ 35 indicates the presence of severe fatigue [36]. See Additional file 1 for an overview of all primary, secondary and exploratory assessments.

The set of secondary outcomes consists of several symptoms, quality of life and level of functioning measured by questionnaires at baseline, after 14 weeks and in follow-up, including depression, HRQOL and anxiety.

Neurocognitive functioning is tested using a standardized clinical test battery that is normally used for clinical care to evaluate preoperative and postoperative cognitive status. It consists of widely used standardized psychometric instruments with published normative data, such as the Stroop Color Word Test [56] and the Rey Complex Figure Test [57].

Furthermore, data about the usage of the online platform are collected, such as the number of logins, start and finish date of a module, completion date of the diaries and the amount of time spent on the platform. Therapists will register the time they invest per patient. Patients’ expectations of intervention outcome [58] and their satisfaction with the intervention and the platform [59] will be assessed before and after the intervention, respectively.

### Exploratory measurements

At baseline and after 14 weeks several exploratory measurements will be conducted, see Additional file 1 for an overview. These measurements are used to identify possible biomarkers for intervention success.

Brain connectivity and network topology will be assessed with magnetoencephalography, resting-state functional MRI, and diffusion MRI. Magnetoencephalography provides a non-invasive tool to study the brain’s neuronal networks and functional connectivity [60, 61]. Properties of baseline network topology of the brain may predict outcome of CBT [34, 35].

Furthermore, patients will undergo neurological examination, using the Neurologic Assessment in Neuro-Oncology Scale [62]. This is a standardized method of neurological physical examination in neuro-oncology patients and an objective clinician-reported outcome of neurologic function.

